### Economics of obesity

There is a large literature in economics that finds that heavier individuals are less likely to be employed and, when employed, tend to earn less (see e.g. Cawley, 2004; Averett, 2011). (This disadvantage is greater for women than men). Some studies have been conducted that seek to measure whether this relationship is causal; that is, whether being heavier lowers wages. These studies rely on natural experiments, which have some advantages but also have the disadvantage that they are not based on a randomized controlled trial. In this study we will also seek whether weight loss is followed by improvements in employment and wages or salary. In addition, we seek to measure the mechanism of any such changes: specifically, whether the weight loss results in fewer days missed due to poor health, or less discrimination in the workplace on the basis of the subject's weight. Collectively, these results will greatly improve our understanding of whether weight lowers employment and wages, and if so, whether it is due to poor health or employer discrimination.

### Can practitioners predict who will do well at weight loss?

Many practitioners will have an intuition of those who will do well on a weight loss programme or those who may not lose weight. However it is not known whether such intuition is valid or whether it is misconceived. This intuition is based on the behaviour of participants and therefore it is important to identify what factors are taken into account to make this judgement. As an observational study it will be determined whether practitioners intuition predicts weight loss and what factors influence this perception.

### Effect of weight loss on cognitive function

A recent meta-analysis reported that obesity in mid-life is associated with lower brain volume and that it also increases the risk of Alzheimer's disease and vascular dementia by nearly 100% (Loef, 2013; Meg, 2014). Despite evidence showing that obesity-related neuro-cognitive risk factors (for example, deficits in working memory, learning, psychomotor speed and executive function) can lead to dementia, literature investigating if neuro-cognitive functions are altered after undergoing a weight loss intervention is sparse.

A recent systematic and meta-analytic review which investigated the effectiveness of intentional weight loss on cognitive function in overweight and obese adults identified the possible mechanistic role of insulin resistance in cognitive decline. Greater insulin resistance was associated with an Alzheimer disease-like pattern or reduced cerebral glucose metabolic rate in adults with pre-diabetes or newly diagnosed type 2 diabetes mellitus (Siervo, 2011). Therefore, lifestyle weight loss interventions may be effective strategies to improve cognition and, therefore, prevent Alzheimer disease, but further studies are warranted to establish this link. The authors of this review (Siervo, 2011) also

noted a lack of randomised controlled clinical trials (only two) in this field, and that stability of improved cognitive function following weight loss had not yet been investigated. Hence, it is unknown whether the beneficial effects of weight loss can be extended to improvements in cognitive function and is an area that warrants further research.

With respect to the specific complementary medicines being investigated in this trial, ginseng has shown promise of a cognitive enhancing effect (Lee, et al., 2008), but recent systematic reviews have highlighted the need for randomised, double-blind, placebo-controlled trials with large sample sizes to investigate the effect of ginseng in different populations (Geng et al., 2010; Lee et al., 2009).

This proposed research outcome will assess the change in cognitive function between groups and the association between weight loss and cognitive function. This study will also investigate weight loss responders ( $\geq 5\%$  of weight loss, and  $\geq 10\%$  of weight loss) to those who lose no weight ( $0 \pm 1\%$ ), to establish whether there is a certain weight loss that corresponds to improvements in cognitive function. The research in this field is sparse and this will be a world first pilot study conducted in those with obesity and pre-diabetes with a longer-term follow-up of 12 months.

#### Association of diet and oral health in obesity.

Periodontitis is a silent or asymptomatic condition, characterized by destruction of periodontal tissues and ultimately loss of teeth (Dye, 2012). It is associated with various chronic conditions (diabetes mellitus, cardiovascular diseases and aspiration pneumonia) and has a negative impact on a person's quality of life (Buset et al., 2016, Genco and Genco, 2014). The prevalence of periodontitis in the Australian population is reported to be 24.5% (Roberts-Thomson and Do, 2007).

Obesity is also a risk factor for periodontitis (Suvan et al., 2011, Nascimento et al., 2016) and is associated with increased levels and proportions of periodontal pathogens, especially in patients with periodontitis (Maciel et al., 2016). However, the explanatory factor between obesity and periodontitis is yet to be discovered. Obese individuals with periodontitis have increased levels of pro-inflammatory cytokines as compared to obese individuals without periodontitis and non-obese individuals (Zimmermann et al., 2013, Pradeep et al., 2015).

Diet is a modifiable risk factor for obesity (El Ghoch et al., 2016). We hypothesize that diet is associated with both obesity and periodontitis, influences the composition of dental plaque microflora and helps to explain the association between obesity and periodontitis.

### 3 Objectives

#### Primary Objectives

1. To determine the efficacy of FBCx (a formula based on  $\alpha$ -cyclodextrin (marketed under the trade name FBCx)) on cholesterol control in an overweight or obese group with pre-diabetes.
2. To investigate the efficacy of Ginst15 (a ginseng extract formula based on Compound K) on glycaemic control in an overweight or obese group with pre-diabetes.

#### Secondary Objectives

1. The effect of each product and the combination of products absolute on weight loss (kg) and percentage of weight loss, relative to baseline body weight.
2. To examine the changes in full lipid profile (including total cholesterol, high-density lipoprotein (HDL), low-density lipoprotein (LDL)), apolipoprotein B, plasma glucose, and glycated haemoglobin (HbA1c) between groups.
3. To compare the percentage of Participants in each category of glucose tolerance (normal, impaired fasting glucose, and type 2 diabetes) between groups at study completion.
4. To examine changes in body composition by waist circumference, fat mass, fat free mass, and blood pressure between groups.
5. To examine the changes in other biochemical parameters (liver enzymes and inflammatory markers) between groups.
6. To measure the side effect profile of each product using adverse event (AE) reporting.
7. To investigate the change in vitality between groups using the vitality scale of the short form (SF) SF-36 Health Survey.
8. To investigate the relationship between goals, outcome-expectancies, self-efficacy, commitment and weight change across all groups
9. To investigate the relationship between unmet goals, effort, dissatisfaction and weight change across all groups.
10. To investigate the effect of the intervention type on changes in personality (Five Factor Model, self-efficacy) and preferences (risk and time).
11. To investigate whether efficacy of the intervention type depends on the change in personality/preferences.
12. To determine the cost-effectiveness of each intervention relative to the lifestyle programme alone by measuring the cost per quality adjusted life year (QALY).

13. To determine whether weight loss results in better financial outcomes for Participants
14. To measure the change in gut hormones and adipokines between groups.
15. To investigate the long-term outcome of the gut microbiota profile between all groups.
16. To compare the metabolic activity of gut microbiota between groups (short chain fatty acids (SCFA) production in plasma and faeces).
17. To investigate the dynamics of the microbiota community as a result of dietary supplementation and elimination of FBCx and Ginst15 across all groups.
18. To determine the difference in handgrip strength throughout the study.
19. To determine circulating hormones or factors that influence muscle mass or strength, such as but not limited to insulin like growth-factor 1 (IGF-1), IGF-1 binding proteins and cortisol.
20. To evaluate the efficacy of three follow up programmes in preventing weight regain after a weight loss phase.
21. To identify the behavioural strategies people use and the psychological processes that enable them to adopt weight management behaviours (prompted by regular self-weighing).
22. To determine whether practitioners' intuition predicts weight loss.
23. To measure the change in cognitive function between groups and by weight loss achieved (0±1%, 5-10%, >10% weight loss).
24. To identify if a change in diet modifies the oral health in obese people.

#### 4 Study Design

The study will be a single site Investigator initiated and designed, double blinded, randomised controlled trial conducted in Sydney, Australia.

The Boden Institute will recruit 400 evaluable Participants. Recruitment will take place through the existing Boden Institute database via email, the Sydney Local Health District (SLHD) intranet, the University of Sydney website, the SFI Research Study website (Participants will be required to complete the “Australian Type 2 Diabetes Risk Screening Assessment Tool” (Appendix R) to determine their pre-diabetic eligibility), social media, and advertising in local newspapers and radio stations. Participants will also be recruited through editorial pieces, health awareness stands, education sessions, primary care, pharmacies and advertising on the Australian Clinical Trials website.

Due to the number of expected participants and the stringent eligibility criteria of the study, SFI will be assisting with the recruitment through regular newsletters to GPs on their recruitment database, and to Participants who have previously expressed their consent for their details to be kept for future clinical trials (SFI Clinical Registry). Electronic patient recruitment platforms Clariness, Clinlife and Trialfacts will also be employed for participant recruitment.

Interested Participants will be provided with an information sheet containing details on the study (Participant Information Statement).

Potential Participants will be phone screened. The “Australian Type 2 Diabetes Risk Assessment Tool” (Appendix R) and a Participant’s most recent pathology results will be used to determine pre-diabetic eligibility for the study. Providing they do not meet any of the exclusionary criteria, they will then be asked to attend a Screening visit with one of the Investigators. Potential Participants who do not have blood results within the last 6 months will be asked to fast for this visit and a blood sample will be taken.

The potential Participant will give written consent before any procedures are performed. Please refer to “Table 4 - Schedule of procedures” for an exact description of the procedures that will take place at each visit.

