### **6.1 Screening Evaluation (Visit 1) (Day -7)**

At Screening, (1 week prior to Baseline visit), the following measurements and personal history will be recorded:

- Consent
- Height
- Medical history (including any forthcoming procedures)
- Body weight
- Waist circumference
- Electrocardiogram (ECG)
- Blood pressure and heart rate
- Concomitant medications

Medical history should include specific questions on cardiac history, angina, breathlessness, swollen ankles, sleep apnoea, urinary incontinence, impaired fertility, depression, anxiety and functional limitations such as joint pain and decreased mobility.

Their pre-diabetes status will also be confirmed at the Screening visit. The following laboratory samples will be taken:

- Fasting blood glucose
- Glycated Haemoglobin (HbA1c)
- Full lipid profile (total cholesterol, HDL-cholesterol, LDL-cholesterol, total cholesterol: HDL ratio, triglycerides)
- Apolipoprotein B
- High-sensitivity C-reactive protein (hs-CRP)
- Liver enzymes

- Creatinine and eGFR calculation (for those who do not have results within 6 months of Screening)
- Thyroid stimulating hormone (for those who do not have results within 6 months of Screening)
- Full blood count (for those who do not have results within 6 months of Screening)
- Gut hormones and adipokines - ghrelin, leptin, adiponectin, cholecystokinin, glucagon-like peptide-1
- Urine collection (female of child bearing potential)
- Cognitive function tests (substudy)

All Participants in each arm will be given the following:

- Instructions for Stool Specimen Collection
- Stool Collection Kit
- Food Diary
- Accelerometer pedometer

All Participants will be given a food diary that is to be completed prior to attending the Baseline visit. All Participants will be asked to record their dietary intake for three days (2 working days and 1 weekend day).

All Participants will be provided with an accelerometer pedometer, instructed how to use it as this will be used to measure their activity level for five days before the Baseline visit.

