### 6.5.3 Laboratory Safety Testing

Fasting blood samples will be collected from all Participants at Screening, Month 3, 6 and 12. Please refer to Table 6.5.3.1 and Table 6.5.3.2 for an exact description of the sample collected at each visit. Blood samples will be sent to the laboratory for commercial analysis. A small amount of blood plasma (approximately 10 ml) will also be stored in cryotubes in a -80°C freezer and used at a later date for circulating hormones or factors that influence muscle mass or strength, gut hormone and adipokine analysis, and SCFA measurement. These analyses will be performed at the University of Sydney.

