| Supra-gingival plaque                                                     |           | ✓ |           | ✓          |            |

\*For those who do not have results within 6 months of the Screening visit

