### **11.3 Sample Size**

A total of 400 Participants will be recruited into the study. The study is powered for the smallest difference between two of the groups for each outcome, with the larger sample size

being adopted. This also ensures that the sample size is sufficient to determine the effect of the combination treatment (FBCx and GinST15).

FBCx (a formula based on  $\alpha$ -cyclodextrin): Assuming a mean reduction in fasting total cholesterol from baseline of 0.50 mmol/L in the intervention compared to control group, with a standard deviation (SD) of 0.90 mmol/L and an estimated drop-out rate of 15% (at 6 months), a total of 143 Participants would be required to achieve 80% power to detect a difference between the two groups (at a 2-sided significance level of 2.5%).

Ginst15 (a ginseng extract formula based on Compound K): Assuming a mean reduction in fasting plasma glucose from baseline of 0.47 mmol/L in the intervention compared to control group, with a standard deviation (SD) of 1 mmol/L and an estimated drop-out rate of 15% (at 6 months), a total of 200 Participants would be required to achieve 80% power to detect a difference between the two groups (at a 2-sided significance level of 2.5%).

Based on these calculations, 400 Participants (100 in each group) will be recruited and randomised to one of four treatment groups. All randomised Participants will be included in the final analysis.

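### Section 4 limits the Screening fast and blood sample to people without recent results, contradicting the sections that take this only pre-treatment sample from everyone

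*Protocol*

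**What the plan says.** Section 4 (Study Design), in its account of telephone screening, says: "Potential Participants who do not have blood results within the last 6 months will be asked to fast for this visit". The sentence goes on to say that blood will be taken, so the same condition governs the fast and the sample.

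Section 6.5.3 says: "Fasting blood samples will be collected from all Participants at Screening, Month 3, 6 and 12". Section 6.1 introduces its list with "Their pre-diabetes status will also be confirmed at the Screening visit. The following laboratory samples will be taken", and glucose, HbA1c, lipids, apolipoprotein B, hsCRP and the gut hormones follow without any condition. Three items in that list do carry a waiver, worded for the first of them as "Creatinine and eGFR calculation (for those who do not have results within 6 months of Screening"; the other two are TSH and full blood count. The footnote to Table 6.5.3.1, "For those who do not have results within 6 months of the Screening visit", is attached to those same three tests only.

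The sample size in Section 11.3 rests on fasting changes for both products: "Assuming a mean reduction in fasting total cholesterol from baseline of 0.50 mmol/L" and "Assuming a mean reduction in fasting plasma glucose from baseline of 0.47 mmol/L".

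**The concern.** The protocol schedules no glucose or lipid measurement between Screening and the first dose. Table 4 places blood collection at Visits 1, 5, 8 and 12, and Table 6.5.3.1 leaves Visit 2 empty for these tests. Product and diet both start at Visit 2. A poor or missing Screening value therefore cannot be replaced once treatment has begun.

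Section 4 is also the only place that says which people are told to fast for Screening. The other sections say what is collected; none gives the participant that instruction. Entrants with recent results are an expected group, since Section 5.2 accepts results from the 6 months before Screening as evidence of pre-diabetes. Staff who brief such people from Section 4 could have them arrive fed.

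Three analyses in Section 11.4 would feel this:

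- **ANCOVA between treatments.** If baseline is the covariate, as is usual, a fed or missing value weakens the adjustment.
- **Repeated-measures ANOVA within groups.** A fed Screening glucose followed by fasting values at Months 3 and 6 can look like improvement.
- **Lipid subgroups.** If hyper-triglyceridaemia and hyper-lipidaemia are classified on Screening lipids, unfasted values can put people in the wrong subgroup.

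**Working it through.** **1. The passages side by side**

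| Place in protocol | Who gives Screening blood for glucose and lipids | Fasting |
|---|---|---|
| Section 4 | People with no results in the last 6 months | Asked of those people only |
| Section 6.1 | Everyone; only TSH, creatinine/eGFR and full blood count are waived | Glucose is listed as fasting |
| Section 6.5.3 | Everyone | Yes |
| Section 6.5.3.3 | Scheduled at Screening without condition | Glucose is listed as fasting |
| Table 4 | Blood ticked at Screening without exception | Not stated |
| Table 6.5.3.1 | Ticked; no waiver mark on glucose or lipids | Glucose is listed as fasting |

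Section 4 in effect extends a three-test waiver to the whole sample. It cannot be followed together with Section 6.5.3: if only some people are asked to fast, a fasting sample from everyone is not assured.

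**2. The plan's own sample sizes**

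Inputs from Section 11.3: two-sided alpha 2.5%, power 80%, dropout 15%. Formula: n per group = 2(z₁ + z₂)²σ²/δ², with z₁ = 2.241 and z₂ = 0.842, so (z₁ + z₂)² ≈ 9.505.

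- Cholesterol, δ = 0.50, σ = 0.90: 2 × 9.505 × 0.81/0.25 = 61.6, so 62 per group and 124 in total. 124/0.85 = 146; 124 × 1.15 = 143. Stated: 143.
- Glucose, δ = 0.47, σ = 1: 2 × 9.505/0.2209 = 86.1, so 87 per group and 174 in total. 174/0.85 = 205; 174 × 1.15 = 201. Stated: 200.

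Both figures reproduce to within 3%.

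**3. Illustration: participants without a baseline are dropped**

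The documents do not give the share f of participants affected; the values below are assumptions. Power = Φ(δ/(σ√(2/n)) − 2.241), for glucose, with n reduced by the factor (1 − f). After 15% dropout there are 85 per single group, or 170 on each side of a factorial margin.

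| f | Two single groups (85 each) | Factorial margins (170 each) |
|---|---|---|
| 0 | 79.5% | 98.2% |
| 10% | 74.7% | 96.9% |
| 25% | 66.0% | 93.5% |
| 50% | 47.0% | 79.5% |

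**4. Illustration: everyone is kept, but the covariate is weaker for some**

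Let ρ be the correlation between baseline and Month 6, and k the fraction of it that a poor baseline keeps (k = 0 means no usable baseline). Variance ratio = [(1 − f)(1 − ρ²) + f(1 − k²ρ²)]/(1 − ρ²). All three inputs are assumptions. With f from 20% to 60%:

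- ρ = 0.6, k = 0: (0.8 × 0.64 + 0.2)/0.64 = 1.11, up to (0.4 × 0.64 + 0.6)/0.64 = 1.34.
- ρ = 0.6, k = 0.7: 1.06 to 1.17.
- ρ = 0.7: 1.19 to 1.58 for k = 0, and 1.10 to 1.29 for k = 0.7.

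Applying even the extreme ratio of 1.58 to the Section 11.3 variances leaves power on the factorial margins at about 89% for glucose and 97% for cholesterol.

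**The case against.** The strongest reply is that the protocol already requires the right sample. Five places provide for Screening blood from everyone, and Section 4 itself refers the reader to Table 4 for the exact procedures at each visit. The disputed sentence closes a passage on recruitment and eligibility. It says what happens to people without results and does not expressly exempt the others. This largely stands: an absent baseline requires one sentence to override five other places. It does not dispose of the fasting problem, because Table 4 is silent on fasting and Section 4 alone says who is asked to do it.

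A reader might infer more than the documents support:

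- **That outside values up to 6 months old become the analysis baseline.** No passage says so. The 6-month window in Section 5.2 concerns eligibility.
- **That the treatment effect is biased.** Having recent results is fixed before randomisation, so poorer baselines fall evenly across arms in expectation. The loss is precision, not validity.
- **That the endpoints are defined as fasting change from baseline.** Section 11.2 speaks only of cholesterol and glycaemic control. Fasting change appears as a sample-size assumption in Section 11.3.
- **That a definite loss of power follows.** The calculations above rest on assumed shares and correlations, and Section 11.3 claims no gain from a covariate.

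**Conclusion.** The contradiction is real, and it bears on the baseline of both primary outcomes. If staff follow Section 4's instruction on fasting, participants with recent outside results can have an unfasted Screening value for glucose and lipids; on the most literal reading they have no study value at all. Neither can be recovered after treatment starts. The harm is reduced precision in the between-arm analysis, with possible distortion of within-group change and of the lipid subgroups.

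Its size cannot be derived from the documents, which give neither the share of entrants with recent results nor the correlation between baseline and follow-up. The illustrations suggest a modest effect if each product is tested on the factorial margins, and a material one if single groups are compared, where glucose power is already 79.5% before any loss. The conclusion that a correction is needed does not depend on those figures. It rests on the conflicting passages and on the absence of a second pre-treatment draw.

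**What to change.** Reword the Section 4 sentence so that every participant attends Screening fasting and gives the Section 6.1 panel whatever earlier results exist, apart from TSH, creatinine/eGFR and full blood count where the existing waiver applies. Add that this fasting Screening sample is the baseline for both primary outcomes. Leave the use of outside results for eligibility in Section 5.2 as it is; restricting them to telephone pre-screening would remove that route and is not needed here.

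The cost is small: participants with recent results must fast for one morning. No extra draw is needed, because Sections 6.1 and 6.5.3 already schedule it for everyone.
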